## Abstract

**Simple Summary:**

Relationships between drug concentrations in blood and efficacy and/or toxicity have been reported for up to 80% of oral anticancer drugs (OADs). Most OADs exhibit highly variable drug concentrations at the approved dose. This may result in a significant proportion of patients with suboptimal drug concentrations. Therapeutic Drug Monitoring (TDM), which is dose optimization based on measured drug concentrations, can be used to personalize drug dosing with the overall goal to improve the benefit-risk ratio of anticancer drug treatment. The ON-TARGET study aims to investigate the feasibility of TDM in patients receiving either axitinib or cabozantinib for the treatment of renal-cell carcinoma with the main objective to improve severe tyrosine kinase inhibitor associated toxicity. Additionally, the feasibility of volumetric absorptive microsampling (VAMS), a novel minimally invasive and easy to handle blood sampling technique, for TDM sample collection is investigated.

**Abstract:**

Exposure-efficacy and/or exposure-toxicity relationships have been identified for up to 80% of oral anticancer drugs (OADs). Usually, OADs are administered at fixed doses despite their high interindividual pharmacokinetic variability resulting in large differences in drug exposure. Consequently, a substantial proportion of patients receive a suboptimal dose. Therapeutic Drug Monitoring (TDM), i.e., dosing based on measured drug concentrations, may be used to improve treatment outcomes. The prospective, multicenter, non-interventional ON-TARGET study (DRKS00025325) aims to investigate the potential of routine TDM to reduce adverse drug reactions in renal cell carcinoma patients receiving axitinib or cabozantinib. Furthermore, the feasibility of using volumetric absorptive microsampling (VAMS), a minimally invasive and easy to handle blood sampling technique, for sample collection is examined. During routine visits, blood samples are collected and sent to bioanalytical laboratories. Venous and VAMS blood samples are collected in the first study phase to facilitate home-based capillary blood sampling in the second study phase. Within one week, the drug plasma concentrations are measured, interpreted, and reported back to the physician. Patients report their drug intake and toxicity using PRO-CTCAE-based questionnaires in dedicated diaries. Ultimately, the ON-TARGET study aims to develop a nationwide infrastructure for TDM for oral anticancer drugs.

## 1. Introduction

The development of targeted oral anticancer drugs has significantly improved not only the number of treatment options, but also the prognosis for many tumor entities. Over the last decade, the route of administration has changed from intravenous to oral. This comes with several advantages, such as reduced patient burden due to venipuncture as well as reduction of healthcare costs and a higher flexibility for the patients, as they have to visit their treatment center less often. However, there are also disadvantages: oral anticancer drugs are often administered in complex dosing regimens that are now under the responsibility of the patient which makes the correct intake challenging. Moreover, as patients see their treating physician less often, potential problems such as frequent or severe toxicity or non-adherence might not be identified early on. The majority of targeted oral anticancer drugs displays high pharmacokinetic variability [1,2,3] which results in considerable interindividual differences in the observed drug concentrations after intake of the same dose. Even though exposure-response or exposure-toxicity relationships have been identified for up to 80% of the compounds [3], dosing still mostly follows a “one-dose-fits-all” approach. This fixed dosing results in a significant risk for patients to receive suboptimal (i.e., too high or too low) doses [3,4,5]. Up to 30% of patients with subtherapeutic concentrations have been reported to be at risk for treatment failure while approximately 15% of patients with supratherapeutic concentrations have been reported to be at risk for increased toxicity leading to treatment interruptions or even treatment discontinuation [4]. To prevent therapeutic failure, selecting optimal individual drug doses is crucial.

For drugs with an established exposure-response and/or a exposure-toxicity relationship, measuring drug concentrations in plasma as part of a Therapeutic Drug Monitoring (TDM) framework can be used to detect subtherapeutic concentrations or a high risk for severe or frequent adverse drug reactions due to supratherapeutic concentrations early on [6]. TDM is increasingly being proposed to select optimal individual doses of oral anticancer drugs [7,8,9,10,11,12,13,14,15,16,17]. However, this is usually applied to few patients only, e.g., in the context of clinical trials [3,5] or when they experience particular clinical issues. In ‘traditional’ TDM, drug concentrations are quantified in venous plasma samples [6], requiring the patient to come to the treatment center and undergo venipuncture. As this procedure is time-intensive for both the patient and the treatment team, and venipunctures can be painful, alternative blood sampling methods are increasingly investigated. As a minimally invasive approach, volumetric absorptive microsampling (VAMS), an enhanced development of dried blood spot sampling, allows collecting a small defined volume (10–30 μL) of capillary blood from the patient’s fingertip [18] which is subsequently air-dried and sent to the analytical laboratory using normal post. In contrast to venous blood, using dried capillary blood as matrix for TDM has several advantages: (i) the samples can be collected in a home-based setting [19], (ii) the collected blood samples do not have to be cooled or further processed [19,20], and therefore (iii) the samples can be shipped to the laboratory via normal post [19,20]. The main advantages of VAMS over dried blood spots sampling are the collection of defined blood volumes (10–30 μL), its independence of hematocrit values [18], and its easy handling. The use of VAMS as an alternative to venous blood sampling has already been successfully applied for several compounds such as anti-epileptic drugs [21,22,23,24].

We previously identified a lack of experience and a missing infrastructure as an obstacle to the implementation of TDM for oral anticancer drugs as part of clinical routine [3]. Thus, the observational ON-TARGET study aims to investigate the potential of using routine TDM in clinical practice for reducing the severity and frequency of adverse drug reactions experienced during oral anticancer drug therapy. In addition to the Common Terminology Criteria for Adverse Events (CTCAE) [25], the patients’ perspective of their symptom burden will be assessed in this study by using the Patient-Reported Outcomes version of the CTCAE (PRO-CTCAE) [26] as the CTCAE grading often underestimates the severity and frequency of treatment-related toxicity experienced by patients [27,28,29]. This will further allow exploring the association between drug concentrations and toxicity. Moreover, the study aims to investigate the feasibility, practicability, patient compliance, and acceptance of using home-based VAMS capillary blood sampling as an alternative to venous blood sampling. Ultimately, the ON-TARGET study’s goal is to develop a nationwide infrastructure for routine TDM for oral anticancer drugs.

## 2. Materials and Methods

The ON-TARGET study (short for: Non-interventional study on Therapeutic Drug Monitoring (TDM) in patients with renal cell carcinoma and on the feasibility of using Volumetric Absorptive Microsampling (VAMS) for sample collection) is a prospective, multicenter, non-interventional study (DRKS00025325). Both hospitals and outpatient oncology practices which have implemented TDM as part of their clinical routine can participate as clinical study centers. Patient treatment and prescription of anticancer drugs is at the physician’s discretion and independent from a potential inclusion into the ON-TARGET study. Physicians may propose participation in the ON-TARGET study to (i) patients who experience, or are at high risk of experiencing, frequent and/or severe adverse drug reactions, or (ii) patients for whom TDM could be useful for other reasons (e.g., in the context of suspected non-adherence). The duration of the study participation is at the discretion of the patient and the treating physician.

### 2.1. Inclusion and Exclusion Criteria

Renal cell carcinoma patients at any disease stage receiving either axitinib or cabozantinib in an in-patient or outpatient setting can be included in the study upon provision of their written informed consent. To be eligible for inclusion, patients need to have full legal capacity and be physically, mentally, and based on their verbal skills capable of completing patient questionnaires in German language without the help from a third party. In line with the non-interventional character and to cover a real-world population, patients may be included in the study regardless of their time of treatment start with axitinib or cabozantinib, i.e., both patients already receiving axitinib or cabozantinib and patients starting to receive axitinib or cabozantinib at the time of study inclusion are eligible. In line with the study’s ‘real-world’ setting, patients can be included regardless of their concomitant diseases or co-medication. Furthermore, there is no pre-specified ratio of male/female patients; according to the national cancer database of the Robert Koch Institute in Germany, the 1-year prevalence rate is approximately 1:1.7, which we would also expect to see in our study [30].

### 2.2. Primary Objective

The primary study objective is the prospective evaluation of the potential of routine TDM to reduce the frequency and severity of adverse drug reactions in comparison with the frequency and severity of adverse drug reactions observed in historical controls in renal cell carcinoma patients receiving axitinib or cabozantinib.

### 2.3. Secondary Objectives

Secondary objectives of the study are to identify patient subgroup(s) that experience particularly severe and/or frequent adverse drug reactions. Considering the reported exposure-toxicity relationship for both axitinib [31] and cabozantinib [32], potential plasma concentration thresholds for acceptable toxicity will be explored. Moreover, the feasibility and practicability of using VAMS capillary blood instead of venous blood as matrix for TDM will be investigated.

### 2.4. Study Design

#### 2.4.1. Overview

Patients receiving axitinib or cabozantinib and eligible for inclusion in the ON-TARGET study are approached by their treating physician and informed about the study objectives, the methods applied, and potential risks and benefits associated with the study participation. Patients who are willing to participate must give their written informed consent.

Once a patient has been included in the study, their demographic information, relevant medical history, concomitant diseases, comedication and toxicity are recorded in a dedicated electronic case reporting form (eCRF) during the baseline visit. In addition, they receive one or more patient diary/diaries, depending on the date of the next appointment as each diary covers one month. In these diaries, patients record their daily drug intake along with any optional notes regarding their study treatment and experienced adverse drug reactions. Furthermore, patients complete one PRO-CTCAE questionnaire (see Section 2.4.5) per diary. At the end of each month, patients send their completed diaries to the ON-TARGET coordinating site.

Patients are asked for up to two TDM samples, depending on the study phase (more detailed information in Section 2.4.2 and Section 2.4.3), obtained at a random time during the dosing interval at each study visit. In line with the non-interventional study design, which only allows for blood samples to be obtained as part of standard care, the samples are collected at a single time during the patient’s visit at a treatment center at which TDM is part of clinical routine. Both the last time of drug intake and the time of blood sample collection are documented to derive the time of sample collection within the dosing interval (more detailed information on the evaluation and interpretation is provided in Section 2.4.5). Shipment of VAMS samples occur within 24 h–48 h of sample collection. At the bioanalytical laboratories, concentrations of axitinib or cabozantinib are quantified using methods validated according to the current EMA guidelines [33] and communicated to the pharmacometrics team. The drug concentrations are evaluated, interpreted, and reported back to the treating physician within one week. In line with the non-interventional character of the study, no formal dose recommendations can be made. Drug concentrations are additionally used for evaluating and updating the pharmacokinetic/pharmacodynamic (PK/PD) models. Additional information on cancer disease and any potential change in concomitant diseases, comedication and toxicity is collected. Moreover, exploratory exposure-toxicity analyses for the efficacy biomarkers soluble vascular endothelial growth factors 2 and 3 (sVEGFR2 and sVEGFR3, respectively) [34,35] will be performed. A graphical overview of the study framework is shown in Figure 1.

#### 2.4.2. First Study Phase

In the first study phase, patients are asked to provide both a venous blood sample and a capillary blood sample during their routine visits. For the venous TDM sample, a small volume of approximately 2.7 mL will be separated from the venous blood collected for routine clinical chemistry parameter checks during routine visits. The TDM samples are centrifuged and the plasma aliquoted in 0.5 mL samples for the TDM and biomarker analyses. The capillary TDM samples are collected via volumetric absorptive microsampling using the CE-certified MITRA-VAMS^TM^ (Neoteryx, Torrance, CA, USA) sampling devices. In total, 40 sample pairs are needed to calculate a drug specific conversion factor (capillary blood → venous plasma). This conversion factor is needed for the second study phase, in which home-based capillary blood sampling will be possible (see Section 2.4.3). Assuming that one sample pair will be collected from each patient included in the first study phase, 40 patients will be needed to complete this study phase (see Section 2.5 Statistics). While the first capillary blood sample in the first study phase is always collected by a study nurse, patients will be asked to collect the following capillary blood samples at the treatment center and under the guidance of the study nurses in preparation for the second study phase. This allows ascertaining the correct use of the MITRA-VAMS^TM^ devices and to establish patients’ confidence in using the capillary blood sampling technique.

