#### 2.4.3. Second Study Phase

Both patients who already participated in the first study phase and newly recruited patients can participate in the second study phase. Once drug specific conversion factors have been determined, in line with the real-world design of the study, participants will be able to choose between three TDM blood sampling options: (i) venous blood sampling at the treatment center, (ii) capillary blood sampling at the treatment center, and (iii) capillary blood sampling at home. In option (iii), patients send their capillary blood samples to the bioanalytical laboratories via normal post. After quantification of the drug concentrations in capillary blood, the corresponding drug concentrations in venous plasma are derived by applying the conversion factors determined in the first study phase. To assess the practicability of home-based capillary blood sampling, patients will be asked to complete a short questionnaire on their home-based blood sampling experience, e.g., if they experienced any problems, if they would be willing to use home-based capillary blood sampling again, and which blood sampling technique they would prefer in the future. The home-based collection of capillary blood will allow for samples to be sent to the bioanalytical laboratories in advance of patients’ next control visits, allowing the interpreted results to be ready for discussion at the time of the patients’ next visits.

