### 2.5. Statistics

Based on the exploratory nature of the study, no formal sample size calculations were performed and no formal statistical considerations were made. In general, 30–40 patients per study drug are planned to be included. This number was derived from previous in-house studies, which showed that 30–40 sample pairs (i.e., simultaneous venous and capillary blood sampling) are optimal to identify reliable conversion factors for the calculation of venous drug concentrations from concentrations quantified in capillary blood samples. The usefulness of the TDM will be judged by the participating clinical study centers who are asked to rate the usefulness of the previous TDM on a scale from ‘very helpful’ via ‘somewhat helpful’ and ‘not really helpful’ until ‘not helpful at all’ at each study visit starting from the second visit after the baseline visit. In addition, the study centers are asked if they changed the dosing regimen based on the last TDM result and if yes, in which way (e.g., dose increase or decrease and increase or decrease of the dosing interval). If the dosing regimen was not changed, the study centers are asked to indicate why (e.g., the measured concentration was in the desired range, adverse drug reaction or other). At the end of a patient’s study participation, the study centers are asked to rate the overall usefulness of the TDM for the patient’s treatment. In the second study phase, the proportion of not adequately filled MITRA-VAMS^TM^ devices will be assessed and evaluated. In addition, the duration of shipment and the proportion of lost home-collected VAMS samples will be recorded.

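### The first-phase size of 40 patients in Section 2.4.2 fits neither two drug-specific conversion factors (80 patients) nor the 30–40 patients per drug in Section 2.5

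*Protocol article*

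**What the plan says.** Section 2.4.2 sets the requirement: "In total, 40 sample pairs are needed to calculate a drug specific conversion factor". It then turns pairs into patients, "Assuming that one sample pair will be collected from each patient included in the first study phase", and concludes that "40 patients will be needed to complete this study phase", with a reference to Section 2.5. The 40 patients carry no per-drug qualifier, and no split between the drugs is given.

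Section 2.1 admits "Renal cell carcinoma patients at any disease stage receiving either axitinib or cabozantinib", so there are two drugs, and each patient contributes to one of them. Section 2.4.3 opens the choice of sampling options "Once drug specific conversion factors have been determined", in the plural.

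Section 2.5 states that no formal sample size calculation was made. It then gives its own figure: "In general, 30–40 patients per study drug are planned to be included". It bases this on earlier in-house studies in which 30–40 pairs were found to be optimal for a reliable conversion factor.

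**The concern.** The two sections size the same piece of work, one refers to the other, and their figures differ in two ways. First, 40 is given as the size of the whole phase, although it is derived from the requirement for a single drug's factor. Second, Section 2.4.2 treats 40 pairs as a requirement, while Section 2.5 accepts 30–40. A team that enrols 30 patients per drug meets Section 2.5 and, at one pair each, falls 10 pairs per drug short of Section 2.4.2.

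The conversion factor is at stake. In the second phase it turns a capillary measurement into a venous plasma concentration for capillary samples taken at the centre or at home (options ii and iii in Section 2.4.3). An error in the factor is systematic: it moves all converted values for that drug in the same direction. Venous samples (option i), and the venous results of the first phase, need no conversion and are unaffected.

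**Working it through.** **Inputs**
- Pairs required per conversion factor: 40 (Section 2.4.2).
- Pairs per patient: 1 (assumption stated in Section 2.4.2).
- Drugs, and hence factors: 2 (Sections 2.1 and 2.4.3).
- Planned patients per drug: 30–40 (Section 2.5).

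The article gives no variance for the plasma-to-capillary ratio, so only relative precision can be computed.

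**Step 1: reproduce the stated figure.** Patients = pairs per factor ÷ pairs per patient × number of factors. With one factor: 40 ÷ 1 × 1 = 40. This is the stated number, so it is a one-drug figure.

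**Step 2: apply the same formula to this study.** With two factors: 40 ÷ 1 × 2 = 80.

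**Step 3: compare with Section 2.5.** 2 × 30 = 60 and 2 × 40 = 80, so 60–80 patients. A total of 40 is 40/80 = 50% of the number from Step 2, and 40/60 = 67% of the lower end of Section 2.5.

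**Step 4: what a literal total of 40 would give each drug.** The split is not stated. Whatever it is, the less used drug has at most 40/2 = 20 pairs, and both drugs cannot reach 30, because 30 + 30 = 60 exceeds 40. For illustration, with splits that are assumptions:

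| Split | Pairs per drug | CI width relative to 40 pairs, √(40/n) |
|---|---|---|
| 50:50 | 20 and 20 | 1.41 and 1.41 |
| 60:40 | 24 and 16 | 1.29 and 1.58 |
| 70:30 | 28 and 12 | 1.20 and 1.83 |

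The width ratio takes pairs as independent with the same variability at each size, and it ignores the small change in the t quantile.

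**Step 5: the per-drug reading.** If 40 is meant per drug, the total is 80, the upper end of Section 2.5. The remaining gap is 40 against a lower bound of 30, or 10 pairs per drug. At 30 pairs the interval is √(40/30) = 1.15 times as wide as at 40.

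**The case against.** The strongest reply is that 40 is meant per drug. The sentence starts from one drug's factor, derives the patients from it and points to Section 2.5, which counts per drug. On that reading the arithmetic is sound and only a qualifier is missing. This is probably what was intended, and it takes most of the weight off the literal reading. It does not remove the fault: the text names the phase and not the drug, and 40 as a requirement still disagrees with 30–40.

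It can also be said that the study is exploratory and has no formal sample size. That is so, but the point asks for no power calculation, only that two stated numbers agree. Nor is this a matter of condensed reporting, since the article prints both figures.

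Some stronger readings are tempting and are not supported:
- **The phase will close at 40 patients with half its pairs.** Section 2.4.3 ties the sampling options to determination of the factors, not to a headcount. It sets no number of pairs, so it is only a partial safeguard, but early closure is a possibility and not the plan.
- **The factor will be less precise than promised.** No precision is stated anywhere.
- **No places remain in the second phase.** Section 2.4.3 says that "newly recruited patients can participate in the second study phase", and Section 2.5 introduces its range as a general plan, not as a cap.
- **Repeat pairs will count as independent.** Section 2.4.2 says that after the first sample "patients will be asked to collect the following capillary blood samples at the treatment center", but it describes this as preparation for home sampling. Nothing says that repeats count towards 40 or how they would be analysed, and the analysis may be left to a document not shown.

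**Conclusion.** The point holds as an inconsistency in a stated sample-size figure. As a total for the first phase, 40 is wrong as written: Section 2.4.2's own inputs give 80, and Section 2.5 gives 60–80. Read per drug, 40 is compatible with the upper end of Section 2.5, but the qualifier is absent and the mismatch with a lower bound of 30 remains.

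The arithmetic on patient numbers rests only on figures in the article. That at least one drug would have no more than 20 pairs under a literal total of 40 needs only the article's assumption of one pair per patient. The figures of 20 pairs for each drug and an interval about 1.4 times as wide also assume an even split and independent pairs. The absolute width cannot be given, because the variability of the ratio is not reported. The consequence is confined to second-phase capillary results that are converted.

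**What to change.** In Section 2.4.2, state the number of pairs and of patients per drug and in total. Use one figure in both sections: either 40 per drug (80 in total) or 30–40 per drug (60–80 in total). If the range is kept, name the number within it that counts as sufficient, so that there is one threshold. Add that the capillary sampling options open separately for each drug, once that drug's number of pairs from different patients has been reached.

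The cost is wording in two sections, plus a line in Section 2.4.3 if the opening condition is placed there. Choosing 30–40 leaves planned enrolment unchanged. Choosing 40 raises the planned minimum from 60 to 80, which is the top of the present range. Under either choice, any patient without a usable pair would have to be replaced to reach the number.
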